### Intervention Options

#### Tailored Intervention Condition

The intervention options in *GamblingLess: In-The-Moment* are informed by the relapse prevention model [13,15] as well as data from the *GamblingLess* program of research [41,43,115-120]. The intervention options were designed to target the cognitive processes that mark a state of cognitive vulnerability (cravings, low self-efficacy, and positive outcome expectancies) (secondary proximal outcomes) for the occurrence of a gambling episode (primary proximal outcome). The resulting program comprises 53 activities across three tailored intervention options (modules): (1) *Curbing Cravings*, (2) *Tackling Triggers*, and (3) *Exploring Expectancies*. Consistent with more recent conceptualizations of coping strategies explicated by the relapse prevention model, these interventions include cognitive, behavioral, and third-wave (mindfulness and acceptance) strategies [13,15,138]. Cognitive behavioral treatments have the most established evidence base in both face-to-face and mobile treatment of problem gambling [105-107,139,140], with mindfulness-based interventions receiving emerging empirical support [141,142]. The activities in each of these modules are displayed in Multimedia Appendix 2.

The intervention activities were selected based on their appropriateness for repeated delivery, effectiveness in previous research, and previous acceptability feedback [41,43,115,116]. The selected activities were developed for smartphone delivery with a focus on engagement, interactivity, user preferences, participant literacy, inclusiveness, and ease of use, with the aim of encouraging autonomy and creating an aesthetically pleasing design. Activities involved user interaction and gamified using multimedia delivery strategies comprising a combination of video activities, audio activities, personalized feedback, quizzes, open-ended items, and multiple-choice items. All video-based activities were publicly sourced videos from YouTube, with written permission obtained from each creator. To assist participants in selecting an activity appropriate to their current environment or social situation, all activities are labeled as text, video, interactive, audio, or text and image on each menu. Consistent with the pilot study, *GamblingLess: Curb Your Urge* [115,116], most activities take <5 minutes to complete.

#### Intervention Option 1: Curbing Cravings

The *Curbing Cravings* intervention option includes a bank of 10 craving management activities, including psychoeducation, distraction, breathing exercises, progressive muscle relaxation, mindfulness meditation, urge surfing, imagery, cognitive reframing, decisional balance, and planning [13,14]. In the *GamblingLess* trial, participants reported the lowest self-efficacy for high-risk situations related to urges and temptations [41,43]. Despite the delineation between craving and urges described earlier, the term urges was used in all user-facing aspects of the intervention (ie, EMA items and activity content; the intervention title is not user-facing), given anecdotal evidence in the addiction field that this is the most understandable, accessible, and commonly used term in addiction science [143-145].

#### Intervention Option 2: Tackling Triggers

The *Tackling Triggers* intervention option contains 25 activities to improve self-efficacy across 5 types of high-risk situations: financial pressure, unpleasant emotions, social pressure to gamble, testing control over gambling, and conflict with others. Participants in the *GamblingLess* trial [41,43] reported the lowest self-efficacy in these situations (with the exception of urges and temptations, which are targeted separately in the *Curbing Cravings* intervention option). Each situation type comprises a bank of 5 activities designed to increase a sense of competency and mastery by teaching participants to identify, anticipate, plan for, and effectively cope with these high-risk situations [13,14]. These include behavioral (eg, self-monitoring, goal-setting, behavioral substitution, progressive muscle relaxation, psychoeducation, assertiveness training, conflict resolution training, lapse management, and planning), cognitive (eg, cognitive reframing, imagery, and decisional balance), and acceptance or mindfulness (eg, cognitive defusion and mindfulness meditation) strategies [13,14].

#### Intervention Option 3: Exploring Expectancies

The *Exploring Expectancies* intervention option contains 18 activities to redress 3 types of positive outcome expectancies: excitement, escape, and money. These positive outcome expectancies have consistently displayed positive associations with problem gambling severity and gambling-related harm, particularly in Australian adult samples [69,75,76]. Consistent with the relapse prevention model [13], the focus of intervention activities in this intervention was to explore the validity and reality of positive outcome expectancies by contrasting the possible immediate positive consequences with the delayed negative consequences of gambling [146]. Meta-analytic evidence supports the efficacy of such expectancy challenge interventions for alcohol abuse prevention [147]. Each type of expectancy comprises 6 activities, including behavioral (eg, self-monitoring, personalized normative feedback, psychoeducation, progressive muscle relaxation, and behavioral substitution), cognitive (eg, decisional balance, imagery, and expectancy challenging), and third-wave (eg, mindfulness meditation, and cognitive defusion) activities to redress these positive outcome expectancies.

#### No Intervention Control Condition

In the MRT, the no intervention control condition involves participants being delivered a brief encouraging message, after which their interaction with the app will end. This tailored message involves acknowledgment that participants have an urge, low self-efficacy in high-risk situations, or positive outcome expectancies, as well as encouragement to consider doing something to reduce their urge, avoid or cope with high-risk situations, or reduce their expectations. In this condition, the participants are not provided with any intervention activities.

### Decision Rules

The decision rules are illustrated in Figure 1. At each decision point during the 28-day MRT, responses to EMA items assessing craving intensity (tailoring variable 1), self-efficacy (tailoring variable 2), and positive outcome expectancies (tailoring variable 3) are used to determine eligibility for the delivery of the tailored intervention, according to a set of predetermined decision rules (scoring >0 on each tailoring variable). At each decision point, participants who do not exceed the cut point for any of the tailoring variables are not eligible for any intervention. These participants will receive a brief encouraging message and their interaction with the app will end. In contrast, participants who exceed the cut point on one or more of the tailoring variables are eligible for a tailored intervention (ie, curbing craving, tackling triggers, *or* exploring expectancies).

### Microrandomization Protocol

The microrandomization procedure will then be applied, whereby eligible participants will be microrandomized to a tailored intervention condition or no intervention control condition (Figure 1). Overall, the microrandomization procedure will involve eligible participants having a 75% chance of being microrandomized in the tailored intervention condition and a 25% chance of being microrandomized in the no intervention control condition. However, because the reformulated relapse prevention model does not presume that certain factors are more influential than others [15], participants exceeding the cut point on more than one of these tailoring variables will be randomly allocated to a relevant intervention option (curbing cravings, tackling triggers, or exploring expectancies). Specifically, participants who are eligible for 2 intervention options will have a 37.5% chance of receiving either intervention option, and those who are eligible for 3 intervention options will have a 25% chance of receiving any of the intervention options. This microrandomization protocol is fully automated, which guarantees that the administration of treatments and assessment of outcomes are blinded.

Following completion of each EMA, participants who are microrandomized to the no intervention control condition will be sent an encouraging message, and their interaction with the app will end. Participants microrandomized to the tailored intervention condition will be sent to the relevant intervention dashboard, which comprises a menu of intervention activities from which they can select. Specifically, participants who are allocated to the craving intervention will be taken to the craving intervention dashboard and asked to select an intervention activity. In contrast, participants who are allocated to the self-efficacy and expectancies interventions will be asked to select a specific type of trigger or expectation, administered an EMA item specific to their selected trigger or expectation (Multimedia Appendix 3), then taken to the relevant intervention dashboard, and asked to select an intervention activity.

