A microrandomized trial (MRT), a form of sequential factorial design in which every participant serves as their own control, will be used to inform the optimization of this JITAI [93,98]. In this MRT, each participant will be randomized to a tailored intervention condition or no intervention control condition at each decision point across a 28-day period [121,122]. The primary aim of the MRT is to explore whether it is worthwhile to deliver a tailored intervention option at a time of cognitive vulnerability. Specifically, the aim is to explore whether, compared with the delivery of no intervention, the delivery of a tailored intervention reduces the probability of a subsequent gambling episode (primary proximal outcome) and improves craving intensity, self-efficacy, and positive outcome expectancies (secondary proximal outcomes). It is hypothesized that the delivery of a tailored intervention will be more effective than no intervention in reducing the probability of a gambling episode and improving craving intensity, self-efficacy, and positive outcome expectancies by the subsequent EMA. Should data allow, secondary exploratory research questions include the following:

*Which type of intervention option is most beneficial at a time of cognitive vulnerability?* Is the delivery of one intervention option (targeting cravings, self-efficacy, or positive outcome expectancies) more likely to reduce the probability of a subsequent gambling episode than the other intervention options?*Under what conditions is the delivery of an intervention option most beneficial?* How do time-variant (EMA) factors (time of day, time of week, craving intensity, self-efficacy, positive outcome expectancies, psychological distress, impulsivity, subjective alcohol intoxication, readiness to change, gambling availability [financial and location], and social context) and time-invariant (preintervention survey) factors (gambling symptom severity, gambling frequency, gambling expenditure, gender, and age) influence the intervention effect on the probability of a subsequent gambling episode?*How do the proximal effects of intervention options change over time as the treatment progresses?* How does the effect of a tailored intervention on the probability of a subsequent gambling episode change over the course of the 28-day MRT?

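### Automation does not blind the participant-reported proximal outcomes, and the comparator called no intervention is a tailored coping message

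*Protocol article*

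**What the plan says.** **Blinding.** Microrandomization Protocol says that the procedure is fully automated, "which guarantees that the administration of treatments and assessment of outcomes are blinded".

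**What participants see.** The next paragraph of that section describes the two conditions. Those allocated to the tailored intervention "will be sent to the relevant intervention dashboard, which comprises a menu of intervention activities from which they can select". By contrast, "participants who are microrandomized to the no intervention control condition will be sent an encouraging message, and their interaction with the app will end".

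**Who reports the outcomes.** Under Distal and Proximal Outcomes, the primary proximal outcome is a yes/no item in the next momentary assessment, asking whether the participant has gambled since the last check-in. The secondary proximal outcomes (craving intensity, self-efficacy, positive outcome expectancies) are also measured at the next assessment, and the participant answers them.

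**The comparator as named.** Research Questions asks whether, "compared with the delivery of no intervention, the delivery of a tailored intervention reduces the probability of a subsequent gambling episode". The hypothesis there and the Statistical Analyses section use the same name for the comparator.

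**The comparator as delivered.** No Intervention Control Condition: "This tailored message involves acknowledgment that participants have an urge, low self-efficacy in high-risk situations, or positive outcome expectancies", together with "encouragement to consider doing something to reduce their urge, avoid or cope with high-risk situations, or reduce their expectations". It adds: "In this condition, the participants are not provided with any intervention activities".

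**The concern.** The article states two properties that its own description of the design does not support.

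First, it says that outcome assessment is guaranteed to be blinded. For the proximal outcomes the assessor is the participant, who knows which condition was just delivered. A reader relying on the sentence would discount differential reporting as a source of bias when it remains possible.

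Second, it calls the comparator no intervention. What is randomized at an eligible point is the tailored intervention condition against a tailored message that prompts coping. The trial is meant to show whether delivering an intervention at a vulnerable moment is worthwhile, and to guide which options are kept. If the comparison is read as support versus nothing, a null result could be taken to mean that support does no better than nothing. The design does not test that. A positive result, likewise, is a benefit over the message and not over nothing.

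**Working it through.** The point rests on setting sections side by side. No figure in the plan is disputed.

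**Step 1: is outcome assessment blinded?**
- Allocation is automated, so neither staff nor participant can foresee it. This is concealment.
- No staff member allocates, delivers or rates anything behind the proximal outcomes, so staff-side bias is removed there.
- The conditions differ visibly: activity dashboard versus message and end of session.
- Under Intervention Loop, only intervention participants re-rate the targeted item after an activity. Those still above the cut point see that rating compared with their earlier one.
- The same person then answers the outcome items at the next assessment.

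So assessment of the primary and secondary proximal outcomes is not blinded.

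**Step 2: is the comparator no intervention?**
- The control message is tailored, names the vulnerability and encourages action on it.
- The article separately defines a *provide nothing* option, used when the prompt is ignored or snoozed. The control is not that option.
- The intervention side is more than a menu. It includes the activities, the trigger- or expectation-specific item (Microrandomization Protocol), the post-activity item with loop and feedback (Intervention Loop) and the short psychoeducational messages (Other App Features).

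So the contrast is this whole package versus a tailored message without activities.

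**Step 3: can either effect be sized?** Not from the documents. The following figures are hypothetical and show only how sensitive the trial would be.

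Inputs: 120 participants, availability 0.3, outcome probability 0.25 without intervention, relative risk 1.21, randomization probability 0.25 (Sample Size); 3 prompts a day for 28 days (Decision Points). A two-sided 5% test, a constant effect and independent observations are assumed.

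Available points: 120 × 84 × 0.3 = 3,024.

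Var(log RR) = (1 − p1)/(n1·p1) + (1 − p0)/(n0·p0).

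*The plan's own figure.* n1 = 756, n0 = 2,268, p1 = 0.25 × 1.21 = 0.3025. Variance = 0.6975/228.69 + 0.75/567 = 0.00305 + 0.00132 = 0.00437, so SE = 0.066. z = 0.1906/0.066 = 2.88, and power is 82.2% (81.6% by noncentral F, 80.4% by a two-proportion formula). The stated power above 80% reproduces.

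*If the message carried part of the effect.* Assume relative risk 1.21 was planned against true nothing. With 10%, 25% or 50% of the log effect delivered by the message, power falls from 81.6% to about 73%, 58% or 31%.

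*If gambling were under-reported after treated points only.* Assume no true effect, the design's 75% allocation and a control rate of 0.25. The apparent relative risk is 1 minus the omitted share. For 10%: n1 = 2,268, n0 = 756, variance = 0.775/510.3 + 0.75/189 = 0.00549, SE = 0.074, z = 0.105/0.074 = 1.42. The chance of a significant apparent benefit is about 29%. For 5% and 20% it is about 11% and 83%.

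The two effects act in opposite directions, and none of the assumed shares comes from the documents.

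**The case against.** **The sentence does not say participants are blinded.** Correct. A reader might infer that the article presents the whole trial, or its participants, as blinded; it says neither. Automation does protect against staff influence. What fails is the guarantee for outcome assessment, because participants assess the proximal outcomes.

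**The control content is disclosed.** Also correct. The article describes the message in full and says that no activities are given, so nothing is hidden. Simpler encouraging messages also appear at ineligible points and on leaving the loop. Adding activities to a message is a legitimate contrast for optimizing the app. What stands is that the hypothesis and analysis carry a name that does not describe the condition.

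**Not all outcomes are affected.** A reader might extend the blinding point to every outcome. The distal outcomes are analyzed within group, with no between-condition comparison, so knowledge of allocation cannot bias such a contrast. App-use indices are logged and serve the acceptability evaluation.

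**Differential misreporting is not shown.** It would need the same person to answer a factual yes/no item differently after treated prompts. Payment depends on completing assessments and not on the answers. The bias is possible, not demonstrated.

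**A loss of power is not shown either.** The Sample Size section does not say that relative risk 1.21 was planned against nothing. If it was planned against the trial's own control, there is no dilution. A reader who recalculates with the 75% allocation and relative risk 1/1.21 gets about 71% power at 120 participants. That gap comes from the sample-size inputs, which are a separate matter.

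**Conclusion.** Both statements are wrong as written. The guarantee of blinded outcome assessment does not hold for the primary and secondary proximal outcomes, and nothing elsewhere in the article repairs it. The comparator named in the hypothesis and analysis is a tailored coping message, distinct from providing nothing.

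The conclusion rests only on the article's text and needs none of the hypothetical figures. The size of any bias or dilution is unknown, and so is the net direction. The documents do not support saying that the result will be biased toward the intervention, that the trial is underpowered for these reasons, or that the control condition should be changed.

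Correcting the wording is worthwhile because it changes what a positive or a null result may be said to show.

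**What to change.** Three changes to the text:

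1. Replace the automation sentence with: *allocation is automated and concealed until delivery, and staff are not involved in allocation or proximal outcome collection; participants are not blinded and self-report the proximal outcomes.*
2. State the primary contrast and hypothesis as the tailored intervention condition (activities, loop and feedback) versus a tailored message without activities, and use this in Statistical Analyses and in the report. If the present label is kept as a short name, define it this way where the hypothesis is stated.
3. State that a null result does not show lack of benefit over providing nothing.

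The cost is wording in the protocol and the report. The app, randomization, data collection and analysis model stay as they are.

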### Intervention Loop

Following the completion of an intervention activity, participants are asked to complete the specific EMA item associated with the intervention group to which they were allocated (postintervention EMA item; Multimedia Appendix 3). Their response to the postintervention EMA item is then subjected to the same decision rules used for the time-based EMA. Participants who fail to reach the cut point on this postintervention EMA item will be presented with an encouraging message, and their interaction with the app will end. Participants who exceed the cut point (ie, score one or more) on the specific EMA item will be presented with a feedback message in which their response to their postintervention EMA item is compared with their time-based EMA response on the same item, encouraged to select another intervention activity, and returned to the relevant intervention dashboard. This intervention loop continues until the participant fails to exceed the cut point or closes the app (Figure 1). At several locations within the app, as well as in the welcome email and trial plain language statements, participants are informed that they can stop the loop at any time by closing the app to ensure that they do not adjust their response to break the loop.

### *Provide Nothing* Option

Importantly, a *provide nothing* option is provided for situations in which the participant is unreceptive, support is not required, or the provision of support may be unsafe, inconvenient, or unethical [94-96,98]. Specifically, support will not be offered if participants ignore the push notification prompting EMA completion or press the *snooze* function to indicate that they are currently unable to complete the EMA (which suggests that they are not in a state of receptivity).

### Other App Features

The home dashboard includes quick links to the *Check In Here*, *Get More Support*, and *More* features. The *Check In Here* quick link allows participants to complete an EMA within the allowed 2-hour period and provides an encouraging message when participants attempt to complete an EMA if more than 2 hours have passed since the last notification. The *Get More Support* quick link, which is also available on each of the intervention activity menu dashboards, provides click-to-call and click-to-email functions to Australian and New Zealand helpline and web-based specialist gambling services. This feature allows participants to escalate the support they receive, including immediate crisis support [101]. The *More* quick link provides information about the app, the trial, contact details, the platform’s privacy policy, the plain language statement, profile information, account details, and sign out. Other app features include the *Did You Know?* feature, which delivers brief passive psychoeducational messages related to cravings, self-efficacy, and positive outcome expectancies before the delivery of every intervention activity and the *Pick For Me* feature on each intervention activity menu, whereby the app randomly selects one of the intervention activities on the menu for participants.

